**Patient characteristics**
Age, sex, medical history (including anisometropic amblyopia, strabismic amblyopia, and refractive amblyopia), and duration of treatment for amblyopia
**Ophthalmological examinations**
Visual acuity, intraocular pressure, angle of strabismus, stereopsis test, refractive error, corneal curvature
**VR app group only**
Daily virtual reality (VR) app usage timeVR app–based stereopsis testUsability evaluation
**Control group only**
Daily eye patch usage time
**Other outcomes**
VR app failureAdverse events

### VR App–Based Stereopsis Test

In the VR app group, a stereopsis test will be conducted using the VR app (Figure 3). In this test, 4 spheres are projected to both eyes, with 1 sphere placed directly in front of each eye. One of the 4 spheres will be moved forward along a path perpendicular to the viewing direction, and the participants will be asked to identify which sphere moved. When the sphere moves closer, its size decreases, whereas when it moves farther away, its size increases. This feature prevents the detection of sphere movement based solely on changes in size and ensures that the movement cannot be recognized by a single eye on the side of the moving sphere. This stereotest is a newly developed measure that has not yet undergone formal validation. The results of the VR app–based stereopsis test will be compared with those of the Titmus stereo test [28].

**Figure 3. F3:**
[figure not shown]
Virtual reality (VR) app–based stereopsis test. One of 4 spheres is moved forward along a path perpendicular to the viewing direction, and participants are asked to identify the moving sphere. To prevent detection of movement based solely on changes in size, the sphere is rendered such that its size decreases when approaching the viewer and increases when receding.

### Usability Evaluation

The parents and guardians of patients will respond to a usability questionnaire consisting of 15 fixed-choice statements regarding the VR app. This questionnaire was custom-designed for this study by selecting items from previously published questionnaires that were applicable to smartphone-based apps [30-32] and by adding original items relevant to the present VR app. Therefore, it has not been previously validated and was used for exploratory or descriptive purposes.

The questionnaire will cover 3 domains: game display (8 items), instruction manual (3 items), and overall impression of the parents (4 items), as shown in Textbox 2. In the game display domain, items will evaluate the clarity of background and text colors, the legibility of on-screen text size, the comprehensibility of on-screen text, the visibility of the size of displayed buttons, the comprehensibility of button labels or icons, the recognizability of button locations, the simplicity of operation, and the appropriateness of sound volume. In the instruction manual domain, items will examine the legibility of the manual text, the clarity of the manual content, and the clarity of guidance on operating the VR app. In the overall impression of the parents’ domain, items will assess children’s speed and ease of learning to operate the VR app, children’s ability to use it independently soon after instruction, children’s willingness to continue treatment using the VR app, and parents’ willingness for their child to continue the treatment using the VR app. Each question will be rated using a 5-point Likert scale (1, strongly disagree; 2, disagree; 3, neutral; 4, agree; and 5, strongly agree) [32,33].

Textbox 2.Usability evaluation questionnaire.
**Game display domain**
The colors of the background and text were easy to see.The size of the displayed text was easy to read.The meaning of the displayed text was easy to understand.The size of the displayed buttons was easy to see.The meaning of the displayed labels or icons of buttons was easy to understand.The location of the displayed buttons was easy to recognize.The operation was simple.The sound volume was appropriate.
**Instruction manual**
The text size in the manual was easy to read.The content of the manual was easy to understand.The manual clearly explained how to operate the VR app.
**Overall impression of the parents**
The child was able to learn how to operate the VR app quickly.The child was able to use the VR app independently soon after learning.The child would like to continue treatment using the VR app.The parent would like the child to continue treatment using the VR app.

### Adherence Evaluation

Treatment adherence will be evaluated for VR app usage and eye patch wearing, defined as the ratio of the actual treatment time to the target treatment time. In the VR app group, the target daily treatment time will be 1 hour of VR app usage per day, and the ratio will be calculated by dividing the actual VR app usage time by the total target treatment time (number of participation days in the study multiplied by 1 h). In the control group, the sum of the daily eye patch wearing times prescribed by the physician will constitute the target treatment time. This ratio will be calculated by dividing the actual eye patch wearing time by the total target treatment time throughout the study period.

### Primary Outcome

The primary outcome measure will be that the improvement in BCVA in the amblyopic eye from enrollment to 12 weeks in the VR app group is noninferior to the improvement in BCVA in the amblyopic eye from enrollment to 12 weeks in the control group. This outcome measure will be designed to confirm that the amblyopia treatment effect of the VR-based program is not inferior to that of conventional eye patch therapy. In addition, since previous studies investigating amblyopia treatment using a VR headset have shown a significant treatment effect following 12 weeks of use, comparing BCVA at 12 weeks will enable an efficacy assessment of the VR-based program for amblyopia under standard amblyopia treatment conditions, and thus, the 12-week time point will be adopted [19,34].

### Secondary Outcomes

Secondary outcomes are as follows:

Comparison of BCVA in the amblyopic eye at baseline and at weeks 4, 8, 12, 16, 20, and 24 between and within the control group (eye patch for the sound eye) and the VR app groupComparison of stereopsis in the amblyopic eye at baseline and at weeks 4, 8, 12, 16, 20, and 24 between and within the control and VR app groupsIn the VR app group, stereopsis in the amblyopic eye measured using the VR-based program for pediatric amblyopia will be compared with stereopsis measured using the Titmus stereo test at baseline and at weeks 4, 8, 12, 16, 20, and 24 during clinic visitsComparison of the ratio of total wearing time to target wearing time (treatment adherence) at weeks 4, 8, 12, 16, 20, and 24 between the control and VR app groupsComparison of the angle of strabismus in the amblyopic eye at baseline and at weeks 4, 8, 12, 16, 20, and 24 between the control and VR app groupsIn the VR app group, the association between the VR gameplay status (including game type, play date/time, play duration, and game settings) and BCVA in the amblyopic eye, stereopsis, the ratio of total wearing time to the target wearing time, and ocular deviation will be evaluatedMalfunctions of the VR-based program for pediatric amblyopiaAdverse eventsUsability evaluation (VR app group only)

To evaluate the effects of amblyopia treatment in the control and VR app groups, BCVA in the amblyopic eye will be assessed as secondary outcome 1 and stereopsis in the amblyopic eye as secondary outcome 2. To assess the reliability and validity of stereopsis measurement using the VR app, secondary outcome 3 will involve comparing stereopsis in the amblyopic eye measured using the VR app for pediatric amblyopia with that obtained during clinical visits using the Titmus stereo test. To evaluate treatment adherence in the control and VR app groups, secondary outcome 4 will involve assessing the ratio of the total wearing time to the target wearing time. To evaluate the safety of amblyopia treatment using the VR app, secondary outcome 5 will involve comparing the angle of strabismus in the amblyopic eye between the control and the VR app groups. To investigate how VR gameplay status correlates with efficacy and safety, secondary outcome 6 will involve examining the VR gameplay status in the VR app group (including game type, play date or time, play duration, and game settings) in relation to BCVA, stereopsis, treatment adherence, and ocular deviation. Secondary outcome 7 will evaluate malfunctions of the VR app for pediatric amblyopia, secondary outcome 8 will monitor adverse events, and secondary outcome 9 will assess usability in the VR app group. Adverse events will be monitored throughout the trial. Based on our safety evaluation of the VR app in adults, where no visually induced motion sickness (VIMS) or vision-related adverse events occurred [18], the intervention is not expected to pose major safety concerns. However, careful monitoring remains essential in pediatric populations. Possible adverse events include VIMS, asthenopia, diplopia, transient blurring, and headaches. All adverse events reported by participants or observed during clinic visits will be documented and evaluated for severity and relationship with the intervention. Among the secondary outcomes, those related to BCVA, stereopsis, ocular deviation, and treatment adherence (secondary outcomes 1‐4) have been defined as key secondary end points. Since this is an exploratory clinical study, all secondary outcomes other than the primary outcome will be analyzed and interpreted in an exploratory (hypothesis-generating) manner.

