### Data Collection and Outcome Assessments

The data collection items are listed in Textbox 1. Data on patient characteristics, ophthalmological examination results, VR app malfunctions, and adverse events will be collected from both the VR app and control groups. The daily usage time of the VR app, stereopsis test results obtained via the VR app, and usability evaluation results were collected only for the VR app group. Daily eye patch usage time will be collected only in the control group.

Visual acuity will be measured by BCVA using the Landolt-C chart at a distance [25]. Intraocular pressure will be measured using a noncontact tonometer [26]. The strabismus angle will be assessed using the alternate prism cover test [27]. Stereopsis will be evaluated using the Titmus stereo test [28]. The refractive error and corneal curvature radius will be measured using an autorefractor keratometer [29]. Daily VR app usage time will be calculated from the VR app usage logs, and daily eye patch wearing time will be reported by the patient’s parent in a diary.

Textbox 1.Data collection.

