For between-group comparisons of BCVA, stereopsis, ocular deviation, and the ratio of total treatment time to the target treatment time, 2-tailed *t* tests or repeated-measures mixed-effects models will be used. Within-group comparisons will be conducted with 2-tailed paired *t* tests, repeated-measures analysis of variance, or repeated-measures mixed-effects models. Reliability and validity evaluations of stereopsis measurements using the VR app compared with the Titmus stereo test administered at clinical visits will be performed using 2-tailed paired *t* tests, Cronbach α coefficients, or intraclass correlation coefficients. The associations between VR gameplay status, ophthalmological examination results, and treatment adherence will be examined using multiple regression analyses or mixed-effects models adjusted for confounding factors. The number of adverse events in the control and VR app groups will be compared using the chi-square test. If continuous variables deviate substantially from a normal distribution, more appropriate methods such as the Mann-Whitney *U* test will be applied. A 2-sided significance level of 5% (*P*<.05) and 95% CI will be used for all analyses. We will not apply multiplicity adjustments across secondary outcomes that represent different endpoint domains. However, when repeated measurements of the same outcome are compared at multiple time points (eg, longitudinal analyses of BCVA), appropriate multiple-comparison adjustments (eg, Bonferroni correction or equivalent family-wise error control) will be applied within that end point family. Primary and secondary analyses will follow intention-to-treat, including all data collected before withdrawal. A per-protocol analysis will be performed as supplementary to assess the robustness of the findings.

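### Secondary outcome 6 relates play duration to an adherence ratio built from the same logged play time, so that one association is wholly or partly built in

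*Protocol article*

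**What the plan says.** The Secondary Outcomes section of the protocol article plans, for the VR arm only, to evaluate "the association between the VR gameplay status (including game type, play date/time, play duration, and game settings") on one side, with four outcomes on the other: BCVA, stereopsis, the ratio of total to target wearing time, and ocular deviation. The explanatory text in the same section repeats the pairing: gameplay status is to be examined, including "play duration, and game settings) in relation to BCVA, stereopsis, treatment adherence, and ocular deviation".

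The Adherence Evaluation section defines the ratio for the VR arm: "the ratio will be calculated by dividing the actual VR app usage time by the total target treatment time". The target is "number of participation days in the study multiplied by 1 h", because "the target daily treatment time will be 1 hour of VR app usage per day". On the source of the numerator, Data Collection and Outcome Assessments says: "Daily VR app usage time will be calculated from the VR app usage logs".

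For the analysis, Sample Size and Statistical Analyses states: "The associations between VR gameplay status, ophthalmological examination results, and treatment adherence will be examined using multiple regression analyses". Mixed models are the named alternative, with adjustment for confounders.

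The article does not exempt the pairing of play duration with adherence, and it does not define play duration separately from app usage time.

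**The concern.** The time a child spends playing is listed as an explanatory variable, and it is also the numerator of one of the outcomes. The denominator is set by design at 1 hour per day for every VR child, so it adds no information beyond length of follow-up. A reported link between longer play and better adherence would then largely restate the definition.

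Two things are at stake. First, better adherence is part of the trial's rationale, so a strong coefficient for this pairing could be read as evidence when it is arithmetic. Second, the article names multiple regression. If duration sits in the same adherence model as game type, play date/time and game settings, it takes up variation that those features would otherwise explain, and a real relation between a game feature and use could disappear from the results.

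**Working it through.** The document gives no figure for this association, so there is none to reproduce. The check is algebra from the definition, then simulation to size the cases where the algebra is not exact.

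**Inputs from the protocol article.** 15 VR children; about 20% dropout, which is 0.20 × 15 = 3 children; 24 weeks = 168 days; target 1 h per day.

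**Definition.** For a child with total play time T hours over d participation days, adherence A = T / (d × 1 h).

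**Case 1: play duration is mean daily time.** Mean daily hours = T/d, which equals A. So r = 1 at any dropout.

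**Case 2: play duration is total time, equal follow-up.** A = T/168 for every child, a constant multiple of T. So r = 1. For example, 84 hours gives 84/168 = 0.50.

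**Case 3: play duration is total time, unequal follow-up.** The ratio and the total now separate. A child who leaves on day 84 with 42 hours has A = 42/84 = 0.50, the same ratio as the child above with half the hours. Simulation assumptions: 15 children, adherence drawn from Beta(4,3), 3 early withdrawals with exit uniform over days 28 to 149, exit unrelated to adherence. Mean r is about 0.77 (5th-95th percentile 0.47 to 0.95). With other assumed inputs (Beta(4,4), exit uniform over days 28 to 167, each child at risk of dropout), mean r is about 0.82 at 20% dropout and about 0.70 at 40%.

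**Case 4: play duration is session length.** Adherence is then proportional to session length times session frequency. With the two assumed independent and each uniform on 0.3 to 1, mean r is about 0.68. Session length is a factor of the numerator, so the overlap is partial but does not vanish.

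**Effect on the other gameplay variables.** Assume that the share of time on one game has a true effect of 0.50 on adherence, with residual SD 0.12, in 15 children. The estimated game coefficient for the adherence outcome is:

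| Adherence model | Mean game coefficient |
|---|---|
| Game share only | 0.50 |
| Game share + total duration, equal follow-up | 0 |
| Game share + total duration, 3 early withdrawals | about 0.27 |

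The zero in the second row is exact: duration reproduces the outcome and leaves nothing for game share to explain.

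**Extent.** Four gameplay variables crossed with four outcomes give 4 × 4 = 16 pairings. One of them is circular.

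**The case against.** The strongest reply is that the identity depends on a reading that the text does not fix. Play duration stands beside game type, date/time and settings, which are attributes of a logged session, and the article uses a different term for daily usage. Under a session-length reading the pair is related but not identical. This stands. It rules out saying that the association carries no information under every reading. It does not free the pairing, since part of the association is still built in.

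A second reply is that a condensed list of variables and outcomes is not a model specification, and that which predictors enter which model is normally left to the analysis plan. This also stands in part. The masking of game type, timing and settings is conditional on duration sharing their model, which the article does not state. But the pairing itself is printed twice and sent to regression, so it is stated rather than merely left open.

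Two stronger readings are tempting and lack support. A reader might infer that acuity models will be collinear because duration and adherence both enter as predictors. The article places adherence on the outcome side of secondary outcome 6 and plans no such model. A reader might also infer that the trial cannot answer its own question about gameplay. The stated purpose of this outcome is how gameplay correlates with efficacy and safety. Duration against BCVA, stereopsis and ocular deviation is a legitimate dose-response question and is unaffected.

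**Conclusion.** The point holds, at low severity. The protocol pairs play duration with a ratio that has logged play time as its numerator. The built-in correlation is exactly 1 for mean daily time, and for total time at equal follow-up. In the partial cases it lies at about 0.68 to 0.82 on average for up to 20% dropout, and about 0.70 for total hours at 40% dropout. The exact results follow from the protocol's definition alone. The partial ones rest on the assumed distributions of adherence, exit day, and session length and frequency, and individual trials of 15 children would vary widely around them. The loss of a game effect from 0.50 to 0, or to about 0.27, rests on an assumed effect size and on duration entering the same model.

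Secondary outcome 6 is exploratory and is not among the key secondary endpoints. The primary outcome, the between-arm adherence comparison, the sample size, the significance level and the other 15 pairings are not affected.

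**What to change.** Add one sentence to Sample Size and Statistical Analyses: when the adherence ratio is the outcome, play duration is excluded as a predictor, and game type, play date/time and game settings are kept; play duration remains a predictor for BCVA, stereopsis and ocular deviation.

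It would also help to state in Secondary Outcomes what play duration measures. If the investigators want a duration-type variable in the adherence model, share of time per game is a separate quantity. Session length could be used only with a note that it overlaps partly with the ratio.

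The change needs no new data and leaves sample size and significance level as they are. It should be made before database lock, since all analyses follow it.

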### Sample Size and Statistical Analyses

The primary outcome of this study will be to determine whether the improvement in BCVA from enrollment to 12 weeks in the VR app group is noninferior to the improvement in BCVA from enrollment to 12 weeks in the control group. Based on the assumption that the difference in mean BCVA at 12 weeks between the control and VR app groups will be 0.07 LogMAR [35], the common standard deviation will be 0.14 [36] LogMAR, the noninferiority margin will be 0.10 LogMAR [37], the significance level will be 2.5%, and statistical power will be 90%, a sample size of 24 participants (12 per group) is required [19]. Anticipating a dropout rate of approximately 20%, the target sample size has been set to 30 participants (15 per group).

To assess whether the VR-based program for amblyopia is noninferior to eye patch therapy, the 95% CI for the change in BCVA between 0 and 12 weeks will be calculated for both the control and VR app groups. If the lower bound of the 95% CI for the change in BCVA in the VR app group is greater than that in the control group, the VR-based program for amblyopia will be considered noninferior to eye patch therapy, and the primary outcome criterion will be met.

For between-group comparisons of BCVA, stereopsis, ocular deviation, and the ratio of total treatment time to the target treatment time, 2-tailed *t* tests or repeated-measures mixed-effects models will be used. Within-group comparisons will be conducted with 2-tailed paired *t* tests, repeated-measures analysis of variance, or repeated-measures mixed-effects models. Reliability and validity evaluations of stereopsis measurements using the VR app compared with the Titmus stereo test administered at clinical visits will be performed using 2-tailed paired *t* tests, Cronbach α coefficients, or intraclass correlation coefficients. The associations between VR gameplay status, ophthalmological examination results, and treatment adherence will be examined using multiple regression analyses or mixed-effects models adjusted for confounding factors. The number of adverse events in the control and VR app groups will be compared using the chi-square test. If continuous variables deviate substantially from a normal distribution, more appropriate methods such as the Mann-Whitney *U* test will be applied. A 2-sided significance level of 5% (*P*<.05) and 95% CI will be used for all analyses. We will not apply multiplicity adjustments across secondary outcomes that represent different endpoint domains. However, when repeated measurements of the same outcome are compared at multiple time points (eg, longitudinal analyses of BCVA), appropriate multiple-comparison adjustments (eg, Bonferroni correction or equivalent family-wise error control) will be applied within that end point family. Primary and secondary analyses will follow intention-to-treat, including all data collected before withdrawal. A per-protocol analysis will be performed as supplementary to assess the robustness of the findings.

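### Twelve evaluable participants per group give about 81–84% power at the stated 2.5% level, not 90%, and the direction of the assumed 0.07 logMAR difference is not stated

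*Protocol article*

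**What the plan says.** The first paragraph of Sample Size and Statistical Analyses in the protocol article sets out the whole calculation for the week-12 primary outcome, a noninferiority comparison of the VR app with patching:

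- Hypothesis: the improvement with the VR app "is noninferior to the improvement in BCVA from enrollment to 12 weeks in the control group".
- Assumed effect: "the difference in mean BCVA at 12 weeks between the control and VR app groups will be 0.07 LogMAR". No direction is given.
- Variability: "the common standard deviation will be 0.14" logMAR.
- Margin: "the noninferiority margin will be 0.10 LogMAR".
- Error rates: "the significance level will be 2.5%, and statistical power will be 90" (per cent). Whether the 2.5% is one-sided or two-sided is not stated.
- Conclusion: "a sample size of 24 participants (12 per group) is required", increased to 30 (15 per group) for roughly 20% dropout.

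Further on, the same section sets the general rule for the analyses: "A 2-sided significance level of 5" per cent, with 95% confidence intervals. For a noninferiority question this corresponds to a one-sided 2.5% level.

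**The concern.** Every input is printed, so the number can be checked directly, and 12 per group looks too small for a 2.5% level with 90% power. If so, the trial is credited with a power for its primary outcome that it does not have.

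The missing direction makes this worse. In a noninferiority calculation, the sign of the assumed difference decides whether it is added to the margin or subtracted from it. A total as small as 24 is possible only if the VR app is assumed to be better than patching. A reader is not told this, and so cannot see that the trial has low power in the case where the two treatments work equally well. A failure to show noninferiority could then be read as evidence against the app when the trial was simply too small.

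**Working it through.** **Inputs** (all from Sample Size and Statistical Analyses): SD 0.14, margin 0.10, assumed difference 0.07, level 2.5%, power 90%, 12 evaluable per group. Allocation is 1:1 (Abstract, Methods). Two points have to be supplied by the reader, and both are first taken in the plan's favour: the 0.07 is an advantage for the VR app, and the 2.5% is one-sided.

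**Formula.** With advantage *a* (positive if the VR app is better),

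n per group = 2 (z_α + z_β)² SD² / (margin + a)²

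**Step 1: the plan's figure at the stated level.**
2 × (1.960 + 1.282)² × 0.14² / (0.10 + 0.07)² = 14.25. Rounded up this is 15 per group; with the noncentral t distribution it is 16. The stated 12 is not reproduced.

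**Step 2: which inputs do give 12?**

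| Reading | n per group, unrounded | n per group (normal / t) |
|---|---|---|
| One-sided 2.5%, VR better by 0.07 | 14.25 | 15 / 16 |
| 2.5% taken as two-sided (1.25% per side), VR better by 0.07 | 16.8 | 17 / 19 |
| One-sided 5%, VR better by 0.07 | 11.6 | 12 / 13 |
| One-sided 2.5%, treatments equal | 41.2 | 42 / 43 |
| One-sided 2.5%, VR worse by 0.07 | 457.7 | 458 / 459 |

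All rows are for 90% power. Of the variants tried, only a one-sided 5% level yields 12. That is a plausible source of the figure, but it contradicts both the stated 2.5% and the 95% confidence interval.

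**Step 3: power with 12 evaluable per group.**
The standard error of the difference is 0.14 × √(2/12) = 0.0572. By the normal approximation, power = Φ[(margin + a)/0.0572 − 1.960]. The t results use the noncentral t distribution with 22 degrees of freedom.

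| True difference | Power, normal | Power, t |
|---|---|---|
| VR better by 0.07 | Φ(2.974 − 1.960) = 84.5% | 81.1% |
| Equal | Φ(1.750 − 1.960) = 41.7% | 38.7% |
| VR worse by 0.07 | Φ(0.525 − 1.960) = 7.6% | 7.2% |

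If the 2.5% were two-sided, power with the VR app better by 0.07 would be lower still: 76.8% (normal) or 71.3% (t).

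**Step 4: the dropout step.**
24 / 0.8 = 30, which is correct. If all 15 per group were evaluable, power at the 0.07 advantage would be 91.4% (normal) or 89.4% (t).

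**Step 5: what 90% would need.**
15 to 16 evaluable per group; 15/0.8 = 18.75 and 16/0.8 = 20, so 19 to 20 enrolled per group, or 38 to 40 in total.

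**The case against.** The arithmetic itself is hard to dispute. The serious objections concern scope and remedy.

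- **The equal-effect figure is not an arithmetic error.** Sizing a noninferiority trial on an expected advantage is a legitimate design choice, and the Introduction explains why the VR app is expected to do better. This stands: the 39–42% is a sensitivity result. It belongs in the text because the direction is unstated and the sample size rests wholly on it.
- **The real shortfall may be smaller.** The primary endpoint is at week 12, participation runs to week 24, and the 20% dropout is not tied to week 12. More than 12 per group may therefore contribute; at 14 per group, power is 89.5% (normal) or 87.1% (t). This is fair as a forecast, but the protocol attaches its 90% to 12 per group and adds the other participants to cover losses. They cannot serve both purposes.
- **The written decision rule is not a margin test.** The section's second paragraph compares the lower limits of two separate within-group confidence intervals and never uses the 0.10. Simulated with 12 per group, that rule passes about 87%, 50% and 13% of the time for the VR app better by 0.07, equal, and worse by 0.07. The powers given here therefore describe the test on which the sample size was based, not that rule. The mismatch is a separate defect and does not rescue the 12.
- **The study is called exploratory.** The Secondary Outcomes section applies exploratory interpretation to outcomes other than the primary one. The primary outcome has a formal criterion with a stated level and power.

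**Conclusion.** The concern holds. On the protocol's own inputs, 90% power at a one-sided 2.5% level needs 15 (normal) or 16 (t) evaluable per group, so 30 to 32 in total rather than 24. With 12 per group the type II error is 15.5% to 18.9% instead of 10%. No reading of a 2.5% level makes the stated figures consistent.

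This rests on three assumptions: the 0.07 favours the VR app; the 0.14 is the SD, in each group, of the quantity being compared; and the test is of the between-group difference against the 0.10 margin. The first is the favourable choice; either alternative direction shown above makes the shortfall much larger.

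**What to change.** Keep the target of 30 and correct the statement. Say explicitly that the 0.07 is an assumed advantage for the VR app and that the 2.5% is one-sided, delete the 90% claim, and write, for example:

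> With 12 evaluable participants per group, SD 0.14 logMAR, a noninferiority margin of 0.10 logMAR and a one-sided 2.5% level, a t test of the between-group difference has about 81% power if the VR app is better than patching by 0.07 logMAR, and about 39% power if the two are equal.

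This sentence describes a margin-based test, so the decision rule in the next paragraph has to be brought into line for it to describe the trial's actual criterion.

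The cost is protocol wording only, with a less favourable power figure. If the sponsor prefers to keep 90%, the consistent alternative is to enrol 38 to 40 participants at the same 20% dropout, which means 8 to 10 more children.
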